#### Multidimensional Scale of Perceived Social Support

The Multidimensional Scale of Perceived Social Support, MSPSS [42], is designed to measure satisfaction with social support. It consists of three subscales: the “friends” subscale (which measures support from friends), the “family” subscale (which measures support from family), and the significant others subscale (which measures support from significant others). The MSPSS has previously demonstrated adequate internal consistency in Kenyan adolescents [25].

#### Perceived Control Scale for children

The Perceived Control Scale, PCS [43], includes 24 items related to beliefs about personal control, or the belief that, through effort, one can obtain desired outcomes and avoid undesired outcomes. Example items include “I can make friends with other kids if I really try” and “I cannot stay out of trouble no matter how hard I try.” The PCS has previously demonstrated adequate internal consistency among Kenyan adolescents [25]. We will use the social control and academic control subscales as secondary outcome measures.

#### The Gratitude Questionnaire

The Gratitude Questionnaire (GQ-6) is a six-item questionnaire that measures grateful disposition—the tendency to experience and act with gratitude in everyday life [44]. The GQ-6 has been shown to have strong psychometric properties among North American youths though a previous attempt to use the GQ-6 with Kenyan youths demonstrated weak internal consistency [25].

#### The EPOCH Measure of Adolescent Well-Being

The EPOCH Measure of Adolescent Well-Being assesses positive psychological characteristics that might foster well-being, physical health, and other positive outcomes in adulthood. While the EPOCH has been validated with adolescents in Australia and the USA [45], it has yet to be used with adolescents in Kenya and other sub-Saharan African countries to the best of our knowledge. We will use the Optimism and Happiness subscales of the EPOCH.

#### UCLA Loneliness Scale – shortened version

The UCLA Loneliness Scale is a widely validated tool for measuring trait loneliness. Participants rate their responses to statements such as “I feel isolated from others” and “people are around me but not with me*”* on a 4-point Likert scale. The third and newest edition of the UCLA Loneliness Scale has demonstrated high reliability, construct validity, and discriminant validity [46]. We will use a shortened version of the scale (8-item) of the UCLA Loneliness Scale, which shows similar validity and reliability to the standard 20-item scale [46]. To the best of our knowledge, it has yet to be used with adolescents in Kenya.

#### Program feedback scale

A feedback scale will be used to collect acceptability and feasibility data from participants. The youths will be asked questions about whether they found the program useful, whether they understood the contents of the program, whether they would recommend the program to a friend, which were the most and least helpful elements of the program, and how they would rate their overall experience. They will also have the option to recommend changes to improve the program for future participants. This scale was developed specifically for this study; however, several items were drawn from prior research [13, 47]. The scale is available in Table 3.

**Table 3 Tab3:** Program feedback scale. Items rated on a 1 (“strongly disagree”) to 5 (“strongly agree”) scale unless otherwise specified

I enjoyed/liked participating in the program	
The program as a whole was helpful	
The material in this program was easy to understand	
The homework activities were helpful	
I liked my group leader	
My group leader was helpful	
I agree with this program’s message	
What lesson did you find most useful? If in Shamiri intervention group, options are A) growth-mindset, B) gratitude, V) virtues, and if in study-skills control group, options are A) note-taking, B) effective reading strategies, C) tips for time management, D) study cycle	
What lesson did you find least useful? If in Shamiri intervention group, options are A) growth-mindset, B) gratitude, V) virtues, and if in study-skills control group, options are A) note-taking, B) effective reading strategies, C) tips for time management, D) study cycle	
What was your favorite thing about the program? (free response)	
What do you think we can change to improve the program? (free response)	

#### Timeline for study and data collection

Participant recruitment will begin in mid-to-late June 2019. The intervention will begin in mid-to-late June 2019 and end in mid-August 2019. Data collection will end in December 2019, once final follow-up measures are collected. We intend to report results by the end of 2020. Upon termination of data collection and publication of results, we will make study data publicly accessible at this link [10.17605/OSF.IO/KTW25]. To protect participant confidentiality, we will not provide identifiable data.

### Data analysis plan

#### Sample size and statistical power

Optimal Design (OD) [48], a statistical simulation program for estimating power and sample size for multi-level models, was used to estimate sample size. Based on a pilot study of the Shamiri intervention [13] which revealed an effect size of *d* = .32 for depression and an effect size of *d* = .54 for anxiety, we calculated the sample size necessary to detect an effect of *d* = .3 using an alpha value of *p* = 0.05 and a power of 0.80, accounting for the repeated measures design with five measurement points by specifying settings on OD, and without consideration of covariates or clustering. Using these parameters, at least 200 participants are required per group for a total of at least 400 participants; we aimed to enroll 420 participants. Assuming that 30% of willing students at recruited schools will be eligible to participate in the study—based on previous assessment wherein 30% of youths in 5 participating secondary schools in Kenya showed elevated symptoms of depression and anxiety [13] and projecting that up to 10% of students may discontinue from beginning to midway through the intervention—based on a conservative estimate from the drop-out rates of Osborn et al. [13], at least 1500 youths are needed for baseline screening to realize the minimum sample size. Given the participation of 4 Kenyan secondary schools in the present study with 3200 students enrolled, this sample size is believed to be feasible [13].

#### Interim analyses and stopping guidelines

We do not anticipate problems that are detrimental to the participants during the course of the RCT and subsequent follow-up data collection; as such, we do not have stopping guidelines and do not intend to conduct interim analyses until follow-up data collection is completed.

#### Data description: nesting, missingness, and imputation

There will be four levels of clustering in our data: school (level 4), group-leader (level 3), groups (level 2), and participant (level 1) with repeated measures being the individual observations at the multiple timepoints (level 0). Group leaders and schools will be cross-classified in an unstructured manner as group leaders will be able to lead groups in multiple schools. Groups will be strictly nested within group leaders as participants will be within groups (structured cross-classification). Missing item (measurement) and subject-level data will be imputed twenty times using Fully Conditional Specification (FCS), implemented using the multivariate imputation by chained equations (mice) algorithm in R as described by Buuren and Groothuis-Oudshoorn [49].

#### Analysis of primary and secondary study outcomes

Outcome measures will need to demonstrate internal consistency with Kenyan youths as indexed by a Cronbach’s alpha of at least 0.70 [50] to be considered for further analyses.

Our analyses will follow an intent-to-treat approach, including all participants initially randomized to an intervention condition. We will run a linear mixed-effects model comparing intervention and control groups on each primary and secondary outcome. Models will be organized to reflect the hierarchical structure of the data described earlier with crossed random effects for schools and group leaders and strict hierarchical nesting for observations in participants, participants in groups, and groups in group leaders. All models will include a random intercept that will allow for individual variation at baseline. We will include a random slope that will allow for individual variation in outcome change rates; however, should this result in overfitting (i.e., random effects structure becoming too complex to be supported by the data), we will remove the random slope to allow for more parsimonious models. Time, intervention condition, and their interaction will be included in all models. Covariates will include age (in years) and sex. Age will be included because older adolescents are reported to face increased psychosocial stress, which may exacerbate depressive and anxiety symptoms [25, 51]. Sex will be included because sex differences in internalizing problems have been documented in Kenyan adolescents [24, 25, 29, 52]. We will build two models, one which will include schools a random slope thus allowing for variation in outcome change rates by school, and another with school as a covariate because students in resource-poor schools in Kenya have reported higher anxiety symptoms than students in schools with more resources [25]. We will use Akaike Information Criterion (AIC) to determine which of the two models will be a better fit for the data. Significant (*p* < .05) condition × time interactions in predicted directions will indicate that the intervention condition produced more rapid improvements in outcomes across the full study period (baseline to 4-week endpoint), as compared to the control.

We will calculate effect sizes (ESs) for total pre- to post-intervention change in depressive symptoms (the primary study outcome) using differences in means; these ESs will compare mean gain scores (Cohen’s *d*) reflecting changes in each outcome from baseline to post-treatment for youths in the Shamiri intervention versus study skills control intervention. Statistically significant, positive Cohen’s *d* values will indicate greater improvements for intervention group youths versus control group youths.

Participants who miss one or more intervention sessions will be permitted to attend future sessions. Missing data will be imputed as described earlier. As part of our main analyses, we do not plan to carry out additional analyses such as subgroup analyses to gauge for intervention effects on primary and secondary outcomes. However, we may later conduct additional exploratory analyses (e.g., moderator analyses) in papers separate from those reporting main and secondary trial outcomes.

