#### Randomization, treatment allocation, and blinding

Following baseline assessment and recruitment, youths who meet the inclusion criteria will be randomly allocated within each school to the Shamiri intervention or the study-skills control condition using a computerized random number generator in R Studio. We will use stratified randomization to ensure consistent baseline characteristics (age, form, and sex if mixed school) across groups. There will be no special criteria for discontinuing or modifying allocated interventions. Participants and group leaders will not be blinded to treatment allocation. However, they will not be informed of study hypotheses. To control for possible contamination, the study will be presented to all eligible students as a Wellness and Academic Functioning Program that was intended to improve both academic functioning and wellness. Both conditions will also be of equal duration and will require similar efforts, and group leaders will be instructed to collect study materials at the end of each session (to prevent students from noticing differences in their program materials and learning from others’ materials during the study).

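### The primary model fits a free arm difference at baseline, so the condition-by-time test is a change contrast: valid, but less precise than a baseline-adjusted analysis

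*Protocol article*

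**What the plan says.** Under Analysis of primary and secondary study outcomes, the protocol article sets a linear mixed model for each primary and secondary outcome: "Time, intervention condition, and their interaction will be included in all models. Covariates will include age (in years) and sex". School enters either as a covariate or through a random slope, with the choice made by AIC. A random intercept covers variation between individuals at baseline, so the baseline score is one of the modelled responses. The test is the condition-by-time interaction from baseline to the 4-week endpoint.

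The same section takes the effect size from mean gain scores "reflecting changes in each outcome from baseline to post-treatment".

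On timing, the randomisation section says: "Following baseline assessment and recruitment, youths who meet the inclusion criteria will be randomly allocated within each school". Stratification is by age, form and, in the mixed school, sex. It does not use baseline severity.

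The sample size was found "without consideration of covariates or clustering", and no baseline-to-follow-up correlation is given.

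**The concern.** Baseline is measured before allocation, so randomisation makes the two arm means at baseline equal in expectation. A model with condition, time and their interaction still estimates a separate baseline mean for each arm. The interaction is then a difference between arms in within-person change. The random intercept describes the correlation between a participant's scores, but it does not take a chance baseline difference between arms out of the estimate in the way a baseline adjustment does. Age and sex, as main effects, cannot sharpen a within-person contrast.

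A change score subtracts the whole baseline value. The efficient adjustment subtracts only the part that predicts follow-up. When the slope of follow-up on baseline is below 1, the change score carries extra variance. What is at stake is the standard error of both primary comparisons, and so the power of a trial whose sample size made no allowance for covariates or clustering.

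**Working it through.** **Inputs from the article.** "we calculated the sample size necessary to detect an effect of *d* = .3"; alpha and power from "0.05 and a power of 0.80, accounting for the repeated measures design with five measurement points"; size from "at least 200 participants are required per group for a total of at least 400 participants; we aimed to enroll 420 participants". Alpha is taken as two-sided, because the article does not say.

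**Assumptions.** The correlation ρ between baseline and week 4 is not given, so it is varied from 0.3 to 0.7. Baseline and follow-up SDs are set to 1, and participants are treated as independent.

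**The plan's own figure.** n per arm = 2(1.960 + 0.842)² / 0.3² = 174.4, so 175. With 10% lost, 175/0.9 = 194.4, so 195, which is within 3% of 200. The article, however, applies its 10% ("projecting that up to 10% of students may discontinue from beginning to midway through the intervention") to the number screened: 400/0.9/0.3 = 1,482 against the stated 1,500. A change-score design also gives 200 per arm if 2(1 − ρ) × 174.4 = 200, that is ρ ≈ 0.43. The software's variance settings are not reported, so 200 cannot be called wrong.

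**Variances for the week-4 contrast, per participant.**
- Free baseline effect (change): 2(1 − ρ)
- Common baseline mean or baseline covariate: 1 − ρ²
- Ratio, adjusted to change: (1 + ρ)/2, which is below 1 for any ρ below 1

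Power = Φ(0.3 / √(2 × variance / 200) − 1.96). At ρ = 0.5 the change contrast has SE √(2 × 1.00/200) = 0.100 and z = 3.00. The adjusted contrast has SE √(2 × 0.75/200) = 0.0866 and z = 3.46.

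| ρ | Ratio | Power, change | Power, adjusted | Gain (points) |
|---|---|---|---|---|
| 0.3 | 0.65 | 71.8% | 88.2% | 16.4 |
| 0.4 | 0.70 | 78.2% | 90.5% | 12.4 |
| 0.5 | 0.75 | 85.1% | 93.4% | 8.3 |
| 0.6 | 0.80 | 91.8% | 96.3% | 4.5 |
| 0.7 | 0.85 | 97.2% | 98.7% | 1.5 |

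(Gains are from unrounded powers.)

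**Linear time at weeks 0, 2 and 4 with a random intercept.** With a free baseline effect, week 2 has no weight in the slope, so the power equals that of the change score. With a common baseline mean the variance ratio is 0.60, 0.73 and 0.84 at ρ = 0.3, 0.5 and 0.7. Power goes from 71.8% to 90.4%, 85.1% to 94.0%, and 97.2% to 98.8%.

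**Selection on the screening score.** Let b be the slope of follow-up on baseline. The change-score variance is the residual variance plus (1 − b)² times the baseline variance. Selecting on baseline leaves b and the residual variance alone and shrinks the second term. With b = 0.5 and the baseline variance halved (both assumed), the residual variance is 0.75, the change variance is 0.75 + 0.25 × 0.5 = 0.875, and the ratio is 0.86. ρ falls to 0.38, yet the gain is only about 4 to 6 points, depending on how d is scaled and whether the planned test is set at 80%.

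**Clustering.** With 420 participants in about 48 groups, m = 8.75. Add (m − 1) × ICC to both variances. At ρ = 0.5 and an assumed ICC of 0.05, the ratio moves from 0.75 to 1.1375/1.3875 = 0.82. For a planned test set at 80% power, the adjusted power falls from about 90% to 87%. At a fixed 210 per arm the gain in points hardly changes (74.2% to 82.2%, against 86.7% to 94.4% without clustering), because power starts lower.

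**The case against.** The strongest reply is that nothing here is an error. A growth model with baseline as the first response and a condition-by-time test is conventional, specified in advance and unbiased under randomisation. That stands: this is a point about precision only.

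Stronger readings are tempting, and the documents do not support them.
- **That baseline is ignored because it is not a covariate.** It is in the model as a response. The loss comes from the free condition effect.
- **That the loss is a definite 7 to 10 points, or always above 5.** The article gives no correlation. About 8 points corresponds to ρ near 0.5 at 200 per arm, and at ρ = 0.7 the gain is 1.5. A gain above 5 points across ρ = 0.3 to 0.7 appears only if the planned test is held at 80% power whatever ρ is.
- **That selecting participants on the screening score makes the loss worse.** It lowers ρ, but it also shrinks the baseline variance, and the net effect is a smaller loss. Eligibility rests on either scale, so the degree of restriction is unknown.
- **That chance baseline imbalance is a further harm.** It is already inside the change-score standard error.

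**Conclusion.** The point holds as a matter of efficiency. The planned test is valid but is a difference-in-change contrast, and the effect size has the same form. A baseline-adjusted analysis has smaller variance whenever the slope of follow-up on baseline is below 1. Under equal variances, independence, d = 0.3 and 200 per arm, the gain in week-4 power is about 16 points at ρ = 0.3 and 1.5 points at ρ = 0.7. Under those assumptions the planned contrast falls below 80% only if ρ is under about 0.43. Selection on the screening score reduces the gain, and group-level clustering reduces the proportional saving in variance. Neither removes it in the cases worked. The direction is secure; the size depends on a correlation that the article does not report.

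**What to change.** In the analysis section, choose one of two forms for PHQ-8, GAD-7 and each secondary outcome with a pre-randomisation value:
- keep baseline as a response but drop the condition main effect, so that both arms share one baseline mean; or
- model only the post-baseline scores, with the baseline score and its interaction with time as covariates.

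Do not use both together. Base the effect size on the baseline-adjusted mean difference, not on raw gain scores, and state any correlation assumed when quoting power.

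The cost is a sentence or two of wording. No new data are needed, because the primary baseline scores are the ones that determine eligibility. Since the Trial status section lists the trial as completed, make this a documented change by the route set out under Quality control and trial management, or report it as a labelled sensitivity analysis beside the planned model.

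### Age and sex, and school in one of the two candidate models, are named without a time interaction, so they leave the deciding condition × time test practically unchanged

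*Protocol article*

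**What the plan says.** All references are to the protocol article.

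- **Fixed effects** (Analysis of primary and secondary study outcomes): "Time, intervention condition, and their interaction will be included in all models. Covariates will include age (in years) and sex". No interaction of age or sex with time is named. The reasons given are that older adolescents face more stress and that the sexes differ in internalising problems.
- **School** (same section): two models are to be built. The first lets school act on change: "which will include schools a random slope thus allowing for variation in outcome change rates by school". The second gives school no slope and describes it this way: "another with school as a covariate because students in resource-poor schools in Kenya have reported higher anxiety symptoms". The choice between them is by fit: "We will use Akaike Information Criterion (AIC) to determine which of the two models will be a better fit for the data".
- **Deciding test** (same section): significant "condition × time interactions in predicted directions will indicate that the intervention condition produced more rapid improvements".
- **Allocation** (Randomization, treatment allocation, and blinding): students are randomised within school, and "We will use stratified randomization to ensure consistent baseline characteristics (age, form, and sex if mixed school) across groups".
- **Missing data** (Data description: nesting, missingness, and imputation): missing values are imputed twenty times, so each analysed data set is complete.

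**The concern.** The test is about change, while the covariates, read in the ordinary way, describe level. The section itself supports that reading. Where a term is meant to act on change, it says so (the school slope). Where school is only a covariate, the reason given is a higher level of anxiety.

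Stratified allocation balances school, age, form and, in the mixed school, sex between the arms. To turn that balance into precision for condition × time, the model must let change differ between strata. Neither candidate does so for age, sex or form, and only one does so for school. If the strata differ in how fast symptoms change, that variation stays in the error term and the standard error is wider than it need be. The Study setting section recruits deliberately contrasting schools (national boarding and sub-county day), so differing rates of change are plausible. The sample size was set without allowing for covariates or clustering, so recoverable precision is worth having.

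**Working it through.** **1. Inputs.** From the article: 420 participants, 4 schools, about 48 groups, 12 group leaders, baseline to week 4 with a week-2 midpoint, alpha 0.05, power 0.80. Assumed, because the article gives no figures: variance components, school-slope SDs, and the share R² of the variance of change that the strata explain.

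**2. The plan's own figure.** The article gives no figure for what the covariates contribute. Its 200 per group comes from repeated-measures settings that are not shown. The plain two-sided formula, 2 × 2.8016² / 0.3² = 174.4, gives 175 per group, so 200 can be neither confirmed nor refuted here. Nothing below depends on it beyond the 80% starting power.

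**3. Algebra.** For student i with condition C and time-constant covariates X:

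Y(t) = b0 + b1·t + b2·C + b3·C·t + g·X + u0 + u1·t + e(t)

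The change from week 0 to week 4 is 4·b1 + 4·b3·C + 4·u1 + e(4) − e(0). The term g·X cancels. With complete data at common visits, b3 is estimated from within-student change, which X does not touch.

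**4. Numerical check** (simulated trial of 420, weeks 0/2/4, REML):

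| Participant random effects | Covariate terms | Condition × time | SE | p |
|---|---|---|---|---|
| Intercept | none | −0.277351 | 0.092318 | 0.002662 |
| Intercept | age, sex, school main effects | −0.277351 | 0.092319 | 0.002662 |
| Intercept and slope | none | −0.277351 | 0.101101 | 0.006083 |
| Intercept and slope | age, sex, school main effects | −0.277351 | 0.101101 | 0.006083 |

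The result also held with group and leader intercepts added. With 15% of post-baseline values missing and not imputed, the estimate moved only in the third or fourth decimal (−0.273400 to −0.273261; −0.266804 to −0.266363).

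**5. The school slope does act.** Leaving school out of the model for change widened the SE on average (400 simulated trials each) by 0.8%, 2.8% and 11% for assumed school-slope SDs of 0.15, 0.3 and 0.6 points per week.

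**6. Size of the possible gain.** With strata balanced between arms, covariate × time terms multiply the SE by √(1 − R²). The equivalent number of extra participants is 420·R²/(1 − R²), and power becomes Φ(2.8016/√(1 − R²) − 1.96).

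| R² of change (assumed) | SE factor | Fall in SE | Equivalent extra participants | Power, from 80% |
|---|---|---|---|---|
| 0.02 | 0.990 | 1.0% | 8.6 | 80.8% |
| 0.05 | 0.975 | 2.5% | 22.1 | 82.0% |
| 0.10 | 0.949 | 5.1% | 46.7 | 84.0% |

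In 12 further simulated trials with R² of about 0.14, the SE ratio was 0.930, against √0.86 = 0.927 from the formula.

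**7. The downside.** In the data set of step 4, adding the covariate × time terms raised the SE from 0.092319 to 0.092620 (0.3%) and from 0.101101 to 0.101224 (0.1%).

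**The case against.** The strongest objections, and what stands of each:

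- **School is not confined to level.** A reader might infer that age, sex and school all enter as main effects only, so that the adjustment cannot touch the result. The article does not support this. One candidate gives school a random slope, and step 5 shows that this changes the SE. School as a covariate also takes part in the AIC comparison that picks the reported model. This objection stands, and the point is limited accordingly.
- **Main effect is an inference.** The article never excludes covariate × time terms, and a fuller plan may exist. That is true, but the section's own contrast between a slope and a covariate makes the main-effect reading the natural one.
- **The stated reasons are served.** They concern symptom level, which main effects do model. This stands: the plan does not contradict its rationale. The remaining point is that level is not what is tested.
- **A loss of power is not shown.** It arises only if the strata predict change, and the article gives no such figure. This stands, so the sizes are a range under assumption. The formula also works at participant level. If change varies by group or leader, the proportional gain would be smaller.
- **Sex adds little once school is in.** Three of the four schools are single-sex, so sex is largely aliased with school. This stands and is reflected in the fix.

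**Conclusion.** The point holds in limited form. Age and sex, and school in the covariate candidate, leave the condition × time test practically unchanged; only the school random-slope candidate acts on it. This rests on reading covariate as a main effect and on complete data at common visits, which the planned imputation supplies.

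A reader might go further and infer that the test is biased or that power is certainly lost. Neither follows. Allocation within school and by strata protects against bias, and any excess in the standard error makes the test conservative. The loss is one of precision: modest over the assumed range of R², and essentially nil if the strata do not predict change. It does not invalidate the planned test.

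**What to change.** State one primary model for PHQ-8 and GAD-7, and use it for the secondary scales, in which the stratification factors enter with their interactions with time: time × school (fixed, four schools), time × age, time × form and time × sex. Form is a stratifier but is absent from the present covariates, so its main effect must be added too. Note in the text that, given time × school, time × sex is informed only by the mixed school.

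The cost is a sentence or two and no new data. With time linear there are 7 or 8 interaction parameters: 3 for school, 1 for age, 2 or 3 for form (three or four forms) and 1 for sex. Form main effects add 2 or 3 more. That is small against 420 participants, and the simulated SE penalty when nothing was gained was about 0.1% to 0.3%.

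The Trial status section gives the trial as completed. The change should therefore be documented by the route that Quality control and trial management sets for modifications to analyses, or be reported as a labelled sensitivity analysis beside the planned model.

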#### Study setting

This study will take place in four secondary schools located in Nairobi and neighboring Kiambu Counties, Kenya. Nairobi County is one of 47 geographical counties that act as units of devolved government in Kenya, a low-income country in sub-Saharan Africa. Nairobi is a diverse city with a population of at least 3.2 million that is representative of the cultural and socioeconomic diversity in Kenya [23]. Kiambu County, a county that is part of the former Central Province region, neighbors Nairobi County and has a population of at least 1.7 million [23]. The first author will draw a list of public secondary schools in Nairobi and Kiambu counties. Principals of the schools will be contacted with information about the study and asked to enlist their school to participate. From the pool of interested schools, four schools that have strong demographic, socioeconomic, and educational diversity will be selected. In particular, the selection will be done in such a manner that schools that are ranked as national secondary schools (which have a socio-economically diverse student body from all the regions in Kenya) and sub-county secondary schools (which are often resource-poor day single-sex or mixed secondary schools with student body from the local area) by the Ministry of Education, Science and Technology will be selected—more information on the diversity of secondary schools in Nairobi and Kiambu counties can be seen elsewhere [24, 25]. In total, the final school sample will consist of an all-boys *national* boarding secondary school, an all-girls *national* boarding secondary school, an all-girls *sub-county* day secondary school, and a *sub-county* mixed-day secondary school. This diverse and generalizable sample of high-symptom youth in Kenya will also allow us to conduct robust moderator analyses that can allow us to identify for whom the Shamiri intervention works for.

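### The school term of the primary model is left to an AIC comparison on the trial data, and form, a stratification factor, is in no model; the consequence is modest and the fix nearly free

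*Protocol article*

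**What the plan says.** Under Analysis of primary and secondary study outcomes, the protocol article first describes linear mixed models "with crossed random effects for schools and group leaders". It then sets out two candidates for how school enters. The first is given as "We will build two models, one which will include schools a random slope thus allowing for variation in outcome change rates by school". The second candidate is worded only as "another with school as a covariate". The choice between them is made on the trial data: "We will use Akaike Information Criterion (AIC) to determine which of the two models will be a better fit for the data". The selected model supplies the condition × time test at p < .05. The other adjustment is stated as "Covariates will include age (in years) and sex".

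Under Randomization, treatment allocation, and blinding, participants "will be randomly allocated within each school", and "We will use stratified randomization to ensure consistent baseline characteristics (age, form, and sex if mixed school) across groups". Under Study setting, "This study will take place in four secondary schools located in Nairobi and neighboring Kiambu Counties".

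**The concern.** There are two separate issues.

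**The primary model is not fixed.** Two specifications are open until the outcomes are known, and the same rule is run for each outcome. Nothing requires PHQ-8 and GAD-7 to end with the same model. One candidate needs a slope variance estimated from four schools. The covariate candidate is also unclear, because school is already a random effect in the base structure and the text does not say whether that effect is then removed.

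**The analysis does not carry every factor used to restrict the randomisation.** Age and sex are in the model, each with a reason. School is in both candidates. Form is in neither, and no reason is given. When allocation is balanced within strata, differences between strata largely cancel out of the treatment contrast. If the strata are not modelled, those differences still sit in the residual variance. The standard error is then larger than the design warrants, and the precision that stratifying could have gained is lost.

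**Working it through.** The plan states no figure on this point. The check compares the text and then sizes the consequence.

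**1. Design factors against model terms**

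| Factor | In the randomisation | In the model |
|---|---|---|
| School | yes (allocation within school) | yes, form of the term left to AIC |
| Age | yes | yes |
| Sex | yes, in the mixed school | yes |
| Form | yes | no |

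**2. A slope variance from four schools.** Treated as an idealised variance estimate on 4 − 1 = 3 degrees of freedom, its 95% interval runs from 3/9.35 = 0.32 to 3/0.216 = 13.9 times the estimate. The component can be fitted but is very poorly determined.

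**3. Does the AIC step inflate type I error?** A null simulation used 4 schools × 105 = 420 participants, allocated within school. The SD of level and of slope between participants was 1, and the school SDs were assumed. Models were fitted by maximum likelihood and tested at |z| > 1.96. Group and group-leader clustering and imputation were left out.

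| School SD: level / slope | Runs | Random slope | Covariate | AIC-chosen | Verdicts differ | AIC picks random slope |
|---|---|---|---|---|---|---|
| 0 / 0 | 1,481 | 0.041 | 0.041 | 0.041 | 0% | 43% |
| 0.2 / 0 | 2,102 | 0.047 | 0.047 | 0.047 | 0% | 7% |
| 0.2 / 0.1 | 2,557 | 0.046 | 0.044 | 0.045 | 0.2% | 13% |
| 0.2 / 0.3 | 2,978 | 0.052 | 0.045 | 0.052 | 0.7% | 71% |
| 0.4 / 0.5 | 3,057 | 0.051 | 0.030 | 0.050 | 2.1% | 85% |

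The Monte Carlo standard error at 0.05 is between √(0.05 × 0.95/1,481) = 0.006 and √(0.05 × 0.95/3,057) = 0.004. No inflation is visible. The last column shows that the choice is genuinely open: either model can win.

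**4. Cost of leaving a stratum out of the slope.** Let R² be the share of the variance in change explained by the omitted factor (assumed). The standard error is inflated by 1/√(1 − R²), and the two-sided type I error is 2Φ(−1.96/√(1 − R²)).

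| R² | Standard error too wide by | Type I error |
|---|---|---|
| 1% | 1/√0.99 − 1 = 0.5% | 0.049 |
| 5% | 1/√0.95 − 1 = 2.6% | 0.044 |
| 10% | 1/√0.90 − 1 = 5.4% | 0.039 |

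This agrees with the covariate model in the last simulation row. A school slope SD of 0.5 is a share of 0.25/1.25 = 20%, which gives 2Φ(−1.96/√0.80) = 0.028, against 0.030 simulated.

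**5. Main effect or slope?** The test concerns change within participants, and the participant random intercept absorbs differences in level. With 420 participants, three time points and form explaining 5% or 10% of the outcome variance (assumed; 40 runs each), the ratio of the condition × time standard error without form to that with form as a main effect had a median of 1.000 (range 0.994 to 1.001). A main effect alone therefore gains nothing; the interaction with time is what matters.

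**6. Does the fix work?** In a check on participant slopes, with strong assumed differences in change by school and form, adding school × time and form × time moved the type I error from 0.032 to 0.052. It recovered up to about 5 percentage points of power. Where change did not differ by school or form, the extra terms cost nothing measurable.

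**The case against.** The strongest defence is that this is a limited, pre-stated choice. Both candidates and the criterion are written down, AIC compares overall fit without looking at the treatment p value, and allocation within school means the choice hardly moves the condition × time estimate. That stands, and the simulation supports it. Allowing slopes to vary by school also has a rationale, since the covariate-only model fell to 0.030 when schools differed most in change.

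Four stronger readings are tempting and should not be drawn:

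- **That AIC selection inflates false positives.** This was not shown. The AIC-chosen model stayed between 0.041 and 0.052.
- **That the analysis ignores the randomisation.** Only form is absent. School, age and sex are present, and age probably carries part of form, which is school year.
- **That any effect of form on symptom scores widens the standard error.** Differences in level do not; only differences in change do.
- **That the article is at fault for not saying how AIC is combined over twenty imputed data sets, or whether ML or REML is used.** A condensed article may leave such detail to the analysis plan, which is not shown.

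What survives the defence is that the article itself fixes a rule that leaves the primary model open, and names the adjustment covariates without one of its own stratification factors.

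**Conclusion.** The point holds as a modest improvement, not as a threat to validity. The confirmatory model is undetermined until the data are in and may differ between the two primary outcomes, and form is dropped without a reason.

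The error runs in the conservative direction: a standard error 0.5% to 5.4% too wide, and a type I error of 0.049 to 0.039, if the omitted factor explains 1% to 10% of the variance in change. Those shares are assumed, because the article gives no figure for how change varies by school or form. If change does not vary, the loss is nil. The two school models reached different significance verdicts in at most 2.1% of simulated trials. That result rests on assumed variance components and on leaving out group and group-leader clustering and imputation.

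**What to change.** Delete the AIC step and state one model, used identically for every outcome and every imputed data set:

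- school as a fixed factor plus school × time, replacing the school random effect;
- form plus form × time;
- age and sex as now;
- the group-leader, group and participant structure otherwise unchanged.

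Report the school random-slope model as a sensitivity analysis only.

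The cost is wording and a few degrees of freedom. With time as a single linear term, four schools use 3 + 3 = 6 parameters, and at most four forms use another 3 + 3 = 6. That is at most 12 in all, against a target of 420 participants. The article reports the trial as completed, so the change should go through its own route for documenting modifications to analyses, with a statement of whether it was fixed before the results by arm were seen.
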